### Screening for inclusion

Flowchart of the trial is shown in Figure 1. All 70 to 80-year old women living in the city of Tampere, Finland (n = 9370) were invited to participate in the trial. In addition to willingness, history of at least one fall during the last 12 months and no regular use of vitamin D supplements were the two other primary criteria mentioned in the first contact letter.

**Figure 1 F1:**
[figure not shown]
**Flowchart of the randomized control trial**.

A pre-screening *Health history questionnaire *(information of self-reported health, previous falls, injuries, medication, diseases, and life style factors such as diet, physical activity, smoking and consumption of alcohol) was mailed to 1213 (12.9%) responders who expressed their initial interest and 433 women initially considered eligible for the study were then invited to the medical examination. The inclusion criteria were age between 70-80 years, living at home independently; had fallen at least once during the previous year; no contraindication to exercise; understands the procedures of the study, has been informed of X-ray radiation doses of the DXA and pQCT investigations, and amount of blood samples needed, and voluntarily agrees to undergo all measurements and signs informed consent prior to beginning of the procedure. The exclusion criteria were moderate to vigorous exercise more than 2 hours per week; regular use of vitamin D or calcium + vitamin D supplements; a recent fracture (during preceding 12 months); contraindication or inability to participate in the exercise program; a marked decline in the basic activities of daily living (ADL); cognitive impairments (Mini Mental State Examination, MMSE-test); primary hyperthyroidism; and degenerative conditions, such as Parkinson's disease.

A physician excluded 16 additional women due to exclusion criteria, and 8 withdrew after the baseline measurements leaving 409 eligible women for randomization.

### Randomization

409 participants were randomly assigned into one of the four arms using a computer-generated randomization list (based on simple randomization with random allocation sequence to ensure equal group sizes). The four arms are: 1) exercise + vitamin D (800 IU/d) 2) exercise + placebo 3) no exercise + vitamin D (800 IU/d) 4) no exercise + placebo.

### Participant follow-up procedures

#### Falls

The number of falls will be monitored with daily fall diaries. Diaries will be collected monthly through the mail. Details of each registered fall will be ascertained by the investigator. The definition of a fall is "an unexpected event in which the participant come to rest on the ground, floor or lower level" [45]. Injurious falls are those requiring medical attention and treatment. Minor injuries, such as bruises, edemas, muscular or joint pain, will also be recorded.

### Measurements

All measurements will be done at baseline, at 12-, and 24-month (the end point of the intervention). Blood samples and physical functioning will be assessed also at 6, and 18-month time points.

#### General health status and falls consequences

Information on the participant's health, medication, lifestyle (level of physical activity, use of alcohol, smoking), mobility and cognitive functions will be assessed with appropriate methods. The methods to evaluate functional ability, health-related quality of life (Leipad, Finnish version), fear of falling (Falls Efficacy Scale-International, FES-I, Finnish version) and physical activity (CHAMPS -activities questionnaire for older people) are modified suitable for the Finnish culture.

#### Anthropometry

Body height will be measured to the nearest 0.1 cm, and body weight to the nearest 0.1 kg with a high-precision scale. Body composition (fat mass and lean body mass) will be assessed with dual-energy X-ray absorptiometry (DXA, Lunar Prodigy Advance, GE Lunar, Madison, WI, USA). According to repeated measurements of 22 adults, the *in vivo *precision (coefficient of variation, CV%) was 1.3% for fat mass and 0.7% for fat-free lean mass ([name], unpublished).

#### Bone measurements

Bone mineral content (BMC) of the total body, lumbar spine and left proximal femur (femoral neck and trochanter) will be assessed using dual-energy X-ray absorptiometry (DXA) (Lunar Prodigy Advanced, GE Lunar, Madison, WI, USA). At our laboratory, the in vivo day-to-day precision (coefficient of variation, CV%) of the DXA scanning is better than 1% for the lumbar spine and 1.5% for the proximal femur ([name] 2005, unpublished). In addition to bone mass, strength of the femoral neck will be estimated from the DXA-measurements using the AHA-software.

In addition to the DXA measurements, the tibia will be measured with peripheral quantitative computed tomography (pQCT) (Norland/Stratec XCT 3000, Pforzheim, Germany). The tomographic slices will be taken from the midshaft (50%) and distal part (5% of the tibial length from the distal end plate of the tibia) for assessing bone mineral mass, cortical and trabecular apparent densities as well as strength traits of this weight-bearing bone [46].

#### Physical performance, physical functioning, and physical activity

The maximal isometric leg-extensor strength at the knee ankle 110° will be measured by a strain gauge dynamometer (Tamtron, Tampere, Finland) and the grip strength of both forearms with a standard hand dynamometer (Lafaytte, Loughborough, UK). The participants are verbally encouraged to perform to their maximum and the best performance from three trials will be taken as a test result. Timed up and go test (TUG) [47], Short Physical Performance Battery (SPPB) [48,49] and backwards walking [50,51] will be used for assessing physical functioning. In addition to CHAMPS, each participant's daily number of steps will be measured with a pedometer (Omron HJ-112-E) over the entire 24-month study period.

#### Vitamin D status

Dietary intake of calcium and vitamin D will be assessed with a validated food frequency questionnaire [52] and calculated by Micro-Nutrica software (Social Insurance Institution, Helsinki, Finland). Serum 25-hydroxy-vitamin D (S-25-OHD) will be measured as a marker of vitamin D-metabolism with an OCTEIA immunoenzymometric assay (IDS, Bolton, UK). In addition, serum intact parathyroid hormone (S-iPTH) will be measured (OCTEIA, IDS), as it usually increases when S-25OHD is low, and gives additional information on the severity of vitamin D deficiency. Genomic DNA sample will be taken to find possible gene polymorphism associated with vitamin D metabolism (e.g. the vitamin D receptor, VDR).

#### Plan of analysis

The incidence rate will be calculated as the number of falls divided by the time over which falls are monitored for each participant. The data will be analyzed as a 2 × 2 factorial design and Poisson regression models will be used to estimate incidence rate ratio between the two exercise groups and between the two vitamin D groups for falls and injuries falls. Between-group changes in neuromuscular functioning, physical ability, bone traits, and quality of life will be analyzed by analysis of covariance (ANCOVA) or logistic regression analysis.

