### Outcomes

The primary outcome of the study is the rate of falls and fall-related injuries. Changes in neuromuscular functioning (e.g. body balance, muscle strength), ADL- and mobility functions, bone health, fractures, cardiovascular risk factors, health-related quality of life, fear of falling, depression (WHO-5), cognition (Mini-mental State examination, MMSE) and rate of institutionalization will be analyzed as the secondary outcomes.

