### Sample size consideration

The sample size and power calculations have been estimated for the primary outcome of this study, i.e., the rate of falls. We hypothesized that there will be a 30% difference in the rate of falls between the treatment groups (vitamin D vs. placebo, and exercise vs. non-exercise). The number of women in each group is based on the expectation that the intervention programme (exercise or vitamin D treatment) will reduce the incidence rate of falls by 30% during the two years intervention and the between-group difference will be detected for a given significance level of 0.05 with a statistical power of 80% with a mean treatment time of 1.5 years. The baseline incidence was assumed to be 67 falls per 100 person-years. Accordingly 260 participants needed to be recruited into the study (130 exercisers and 130 non-exercisers, 65 in each group with vitamin D supplement). However, in order to eliminate the role of chance in detecting the possible interaction of vitamin D and exercise, a total number of 400 subjects (100 subjects in each group) were recruited into the study.

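### Poisson regression is fixed for recurrent falls with no allowance for extra-Poisson variation; with model-based standard errors the intervals for total falls would be too narrow

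*Protocol article*

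**What the plan says.** All references are to the Protocol article.

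- **Outcomes:** "The primary outcome of the study is the rate of falls and fall-related injuries".
- **Falls:** "The number of falls will be monitored with daily fall diaries", collected monthly, so one woman can contribute several events.
- **Plan of analysis:** the rate is "the number of falls divided by the time over which falls are monitored for each participant". For the comparison, "Poisson regression models will be used to estimate incidence rate ratio between the two exercise groups". The same model serves the vitamin D comparison and both total and injurious falls, in a 2 × 2 factorial analysis. No dispersion parameter, robust variance, random effect or negative binomial model is named.
- **Sample size consideration:** "The baseline incidence was assumed to be 67 falls per 100 person-years". The intervention "will reduce the incidence rate of falls by 30% during the two years intervention", at a "significance level of 0.05 with a statistical power of 80% with a mean treatment time of 1.5 years". This leads to 260 women, 130 on each side of a factor. The target was then raised to 400 for the sake of the interaction; extra-Poisson variation is not mentioned.
- **Screening for inclusion:** every woman must have fallen at least once in the previous 12 months.
- **Background:** the article notes that most older people prone to falling carry several risk factors.

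**The concern.** An ordinary Poisson model sets the variance of each woman's count equal to its mean. That holds only if women with the same covariates share one underlying fall rate. The Background section gives reason to expect otherwise: women differ in their risk factors, and those at high risk contribute repeated falls. The variance then exceeds the mean, and standard errors taken from the model are too small.

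The point estimate is not at stake, because a Poisson rate ratio stays consistent when the mean model is right. What suffers is the confidence interval, the p-value and the 5% error rate of the primary analysis, on both factorial comparisons. The error runs one way: a chance difference is declared an effect too often.

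**Working it through.** **1. The plan's own sample size.** Inputs from Sample size consideration: control rate 0.67 per year, rate ratio 0.70, mean time 1.5 years, 80% power, 5% significance (two-sided assumed). The formula for Poisson regression with a balanced binary covariate is

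N = φ (1.96·√V0 + 0.842·√V1)² / (T · rate · ln(RR)²), with V0 = 4 and V1 = 2 + 2/0.7 = 4.857.

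With dispersion φ = 1: (3.920 + 1.855)² / (1.5 × 0.67 × 0.3567²) = 33.35 / 0.1279 = 260.8, against the stated 260. The other formulas tried do not match. A rate difference, log rate ratio or square-root comparison gives 147 to 150 per group, and a one-sided test gives 207 in total. The planning figure therefore fits variance equal to mean.

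**2. Dispersion among enrolled women (assumed).** Let each woman have a stable relative risk, gamma distributed with mean 1 and variance v = 0.5, 1 or 2 before selection, and enrol those with at least one fall in the prior year. With r the pre-selection rate and s = 1 + rv, the enrolled group has

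- mean relative risk m = (1 − s^(−1/v−1)) / (1 − s^(−1/v));
- second moment m2 = (1 + v)(1 − s^(−1/v−2)) / (1 − s^(−1/v));
- relative variance k = m2/m² − 1.

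Selection narrows the relative spread. If 0.67 is the enrolled rate, k falls from 0.5, 1, 2 to 0.34, 0.51, 0.69.

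**3. Error rate for total falls.** φ = 1 + k × (enrolled rate × T), and the true error of a nominal 5% test is 2(1 − Φ(1.96/√φ)). Simulated values are in brackets (204 women per side, 4,000 replicates, Monte Carlo standard error up to 0.7 percentage points).

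Reading A, 0.67 is the enrolled rate:

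| v | k | φ, 1.5 y | Error | φ, 2 y | Error |
|---|---|---|---|---|---|
| 0.5 | 0.34 | 1.34 | 9% (8.8%) | 1.46 | 10% (10.5%) |
| 1 | 0.51 | 1.51 | 11% (11.1%) | 1.68 | 13% (12.7%) |
| 2 | 0.69 | 1.69 | 13% (13.6%) | 1.92 | 16% (16.6%) |

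With unequal follow-up averaging 1.5 years (0.5, 1 or 2 years in proportions 1:1:3), simulation gave 10.4%, 12.1% and 14.9%. This is the top of the 9-15% range.

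Reading B, 0.67 is the pre-selection rate, so the enrolled rate is 0.67m:

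| v | Enrolled rate | k | φ, 1.5 y | Error | φ, 2 y | Error |
|---|---|---|---|---|---|---|
| 0.5 | 0.88 | 0.34 | 1.45 | 10% (11.0%) | 1.61 | 12% (11.9%) |
| 1 | 1.07 | 0.53 | 1.85 | 15% (13.7%) | 2.14 | 18% (17.6%) |
| 2 | 1.39 | 0.76 | 2.59 | 22% (22.2%) | 3.12 | 27% (26.2%) |

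Person-level robust standard errors gave 4.6% to 5.6% in all these settings. Under reading A the correct standard error is √1.34 = 1.16 to √1.92 = 1.39 times the Poisson one.

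**4. Injurious falls.** If 15% of falls qualify (assumed), the mean count under reading A at 2 years is 0.15 × 1.34 = 0.20, so φ is only 1.07 to 1.14. Simulated error across both readings and both durations was about 5-8%.

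**5. Power.** For 200 per side over 1.5 years, the variance of the log rate ratio is (1/1.005 + 1/0.7035 + 2k)/200, and power is Φ(0.3567/SE − 1.96). For k = 0 this is 90%. For k = 0.34, 0.51 and 0.69 it is 82%, 78% and 73%.

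**The case against.** The strongest reply is that the article names a mean model and an estimand, not a variance estimator. Nothing in it rules out robust or scaled standard errors, and a condensed article may leave that to a statistical analysis plan that is not shown. This stands in part. A reader might infer that the plan prescribes model-based standard errors. It does not say so; that reading rests on the silence in Plan of analysis and on a sample size that reproduces with dispersion of 1, which is a planning assumption. Still, the model is named without qualification for the primary outcome, and a better specification costs one sentence.

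Four stronger readings are tempting and not supported:

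- *The 5% level is certainly not held.* No dispersion is given, and with none the test keeps its level.
- *The error is generally 17% to 26%.* Those are formula values for variance-to-mean ratios of 2 and 3, ratios the documents do not give. Under reading A the ratio stays below 2. Only reading B with the larger frailty variances reaches that far.
- *Enrolling previous fallers adds to the problem.* Under the gamma model it reduces relative heterogeneity.
- *Both fall outcomes are equally affected.* Injurious falls are too infrequent for much inflation.

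A common rate of 0.67 per year also implies that 1 − e^(−0.67) = 49% of women fall in a year, against the roughly 30% cited in Background. Matching both would need a negative binomial k of about 3.2. The two figures may describe different populations, so this is no estimate for the trial.

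**Conclusion.** The concern holds conditionally and should be fixed. The plan fixes Poisson regression for recurrent counts and provides nothing for extra-Poisson variation. If model-based standard errors are used and women's risks differ, inference on total falls is anti-conservative. The central range is a true error of about 9-15% at 1.5 years and 10-16% at 2 years, rising to about 10-26% if 0.67 per year describes women before selection. For injurious falls it is about 5-8%.

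These figures rest on assumptions that are not in the documents: the frailty variance and its gamma form, a stable personal rate from the prior year into the trial, and a 15% injurious share. The direction of the effect does not depend on the exact values.

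**What to change.** Replace the Poisson sentence in Plan of analysis with one that names, before analysis, a primary method for falls and injurious falls and a sensitivity method:

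- negative binomial regression with log monitored time as offset; or
- Poisson regression with the same offset and person-level robust (sandwich) standard errors.

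Either may be primary, with the other as sensitivity analysis. The Discussion reports recruitment as complete and results as not yet available, so the choice could still be made without knowledge of which interval excludes 1.

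The cost is one sentence and standard software, with no new data and no change of design. Intervals become wider, and real power is lower than the Poisson-based calculation implies: on the assumptions above, 73-82% instead of 90% with 200 women per side at 1.5 years. The sample size section should say so. The increase from 260 to 400, made for another reason, absorbs part of that loss.

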### Intervention

#### Vitamin D supplements/placebo

The participants were randomly assigned to receive placebo (50% of the participants) or 800 IU (20 μg) of vitamin D (50% of the participants) per day for two years. Both participants and outcome assessors are blinded to the group assignment of placebo or vitamin D during the study. At the start, each participant received a pack of pills for six months, and when arriving to the follow-up measurements at six-month intervals the used packs will be returned and new full packs will be given. At this time, compliance will be confirmed by remaining pill counts. A questionnaire on side effects will be administered to all participants at six-month intervals to monitor safety. As standard safety markers, S-Ca and S-Pi will be assayed.

### Training program

Participants randomized to the exercise groups (50% of the participants either on vitamin D or placebo) will attend supervised training classes 2 times a week for the first 12 months, and once a week for the last 12 months of the 24-month intervention. In addition, they receive a home exercise plan to be practised on the rest days.

All group training sessions are supervised by 1 or 2 experienced exercise leaders (physiotherapists). The training program is progressive and consists of strength, balance, agility and mobility training. Main components of the exercise program has been found safe and feasible in the present age group in our previous study [38]. Training sessions are carried out in 8-week periods, either in the exercise hall or gym. Around 10 to 20 participants are expected to attend these training sessions. All training sessions last 60 minutes and include a 10 minutes warm-up as well as stretching for major muscle groups. A 4-week familiarizing period precedes the first 8-week training period to accustom the exercisers to the training, and to familiarize them to each other and the exercise leaders.

During the group exercises in hall, exercises focusing on balance, agility, mobility and change of direction are emphasized. Different surfaces and dual-task situations are employed, especially in balance and agility exercises. In addition to own body weight, ankle weights and vest weights are used in muscle strength exercises. Some exercises will be done with a chair (especially at the beginning of the training) or with a step-board (when advanced). The advanced programs are also aerobic in nature. Exercise programs will either be led by the leaders or implemented as supervised circuit training. Exercise leaders keep a record of the participants' attendance at the group training sessions.

During the gym exercises, resistive equipment is used. All programs include 8-9 different exercises focusing on strengthening large muscle groups: leg extensors (leg press), hip extensors, hip abductors, knee extensors, knee flexors, calf muscles, back muscles, and shoulder and arm muscles. The first gym period begins with 30 - 60% of one repetition maximum (1RM). The target level progresses to 60-75% of 1RM. Two sets of each exercise are done, each set consisting of 8-12 repetitions. The intensity of strength training is assessed using rated perceived exertion (RPE) [53]. The target RPE ranges from 14-18 (12 when starting), and advances progressively. Balance training is included in a short warm-up period.

In addition to supervised training sessions, the exercisers have a home-training program modified from the exercises used during training sessions. During the first year the participants are guided to train at home in the days they do not participate in the supervised group training. In the second year, home-training sessions are recommended at least 3 times a week. One home training session requires 5 to 15 minutes. The exercisers keep a home training diary.

The participants in the non-exercising group (50% of the participants either on vitamin D or placebo) are asked to maintain their current level of physical activity.

### Time schedule

Preparations for recruitment of the participants were completed during the spring 2009. The screening and baseline measurements of the participants began in fall 2009. For practical reasons, the trial started in two phases (201 participants in March 2010 and 208 in March 2011), the follow-up measurements will be carried out in spring 2012 and 2013, respectively.

## Discussion

At the time of writing, recruitment was completed and all participants had been randomized and respective interventions started as planned. The 24-month measurements and the follow-up of the first group will be completed in March 2012, and the second group in March 2013. Results will be available late 2013. Although it is not possible to comment on the effectiveness of the intervention, it is evident that the participants are well committed to the study.
